### Data collection

Detailed clinical procedure-related RRT parameters, and physiologic and laboratory data will be collected. Blood and urine will be collected at baseline, 12, 24, 36 and 48 hr and once daily thereafter until the study participants are discharged from ICU. Data will be collected on standardized case report forms (CRFs). All adverse events will be recorded on the CRF on specific pages reserved for this purpose. A simplified procedure will be used for foreseeable adverse events (hemodynamic instability, rhythm disturbances, electrolyte or acid-base imbalance, and bleeding events related to hemodialysis catheters or anticoagulants). Adverse events will be considered as serious if they cause death, are life-threatening, cause hospitalization (or prolongation of initial hospitalization), cause disability or cause permanent damage, a congenital anomaly or birth defect. Investigators must report any serious adverse event to the sponsor (the University Hospital of Dijon, France) promptly by email or telephone, followed by a written report within 48 hr. Completed CRFs will be returned to the CIC-EC and entered into a secured central database for independent quality control and centralized analysis.

Clinical data obtained will include demographic characteristics, comorbidities and prescribed and current drug therapy. Details of admission diagnoses, surgical status, and dates of hospital and ICU admission will be recorded. Detailed data on AKI and on septic shock will be recorded on the date of enrollment: interventions (i.e. mechanical ventilation, vasoactive drugs and fluid therapy), hemodynamics (i.e. blood pressure, heart rate and central venous pressure), nephrotoxic drugs (e.g. aminoglycosides, radiocontrast agents and hydroxy-ethyl starch), details of sepsis (i.e. site of infection and effectiveness of antimicrobial therapy) and acute physiology (i.e. components of severity of illness and SOFA score, simplified acute physiology score (SAPS II), urine output, fluid balance and secondary non-kidney organ dysfunction). During the trial, data will be collected on daily urine output, fluid balance, electrolytes, acid-base status, serum creatinine and urea, and components of the SOFA score. Data will be collected each day on whether the primary endpoint (mortality) has occurred, for evidence of any secondary endpoints and for criteria for trial discontinuation. Finally, any study protocol violations will be recorded.

All enrolled patients will be followed to determine mortality, continued need for RRT or renal recovery until death or discharge from hospital (whichever occurs first) and at 28, 90, 180 days and 1 year after randomization. Health-related quality of life will be assessed using the EQ-5D form by telephone contact at 90 days and 1 year. The EQ-5D is a generic health-related quality of life measurement instrument comprising five multiple choice questions, and a 100-point overall health state visual analogue scale (VAS) [30]. The questions concern mobility, self-care, daily activities, pain, anxiety and depression. The respondent is required to select one of three ordinal answers best describing their health state in relation to these five domains. Scores are then converted to an overall utility score, with 0 representing death, and 1 representing perfect health.

### Statistical analysis

All enrolled patients will be included in the main population analysis. The primary analysis will be by intention to treat (ITT). The characteristics of the two groups will be compared using the usual univariate tests (chi-squared or Fisher’s exact test for categorical variables, and analysis of variance or Mann–Whitney test for quantitative variables, as appropriate). The main comparison of the proportion of deaths at 90 days in both treatment groups will be performed using Fisher’s exact test, with secondary analysis by the Kaplan–Meier method, comparison using the log rank test, and Cox regression.

For the per-protocol analysis, patients will be grouped according to the time of initiation of the RRT. If RRT is initiated within 12 hr after the onset of the failure stage according to the RIFLE classification, then the patient will be included in the early RRT group. Conversely, if RRT is initiated >12 hr beyond this period, the patient will be included in the delayed RRT group. The per-protocol analysis will use the same techniques as the ITT analysis.

If the ITT and/or per-protocol analyses show a benefit of early (<12 hr) initiation of RRT, a secondary analysis will be performed using an extension of the proportional hazards model proposed by Abrahamowicz and MacKenzie [31] to estimate the non-proportional and non-log-linear effects, taking into account the exact time since initiation of RRT. This model will make it possible to trace the effect of initiation of RRT over time, thus visualizing whether early initiation results in lower risk of death after adjusting for major confounders, taking into account any non-proportional and/or non-log-linear effects. The main conclusion of the test will only cover the ITT analysis. Two interim analyses will be performed after the inclusion of, respectively, 200 and 400 patients.

Safety will be analyzed by assessing the frequency of arterial hypotension requiring the introduction or increase of noradrenaline, pulmonary edema due to overload, cardiac arrhythmias (ventricular tachycardia, ventricular fibrillation, torsade de pointes and atrio-ventricular block grade III), severe metabolic disorders and blood transfusions (≥3 units of packed red blood cells) in both groups and comparing rates using the appropriate tests, with an alpha risk set at 0.05.

The frequency of death within 90 days after randomization will be recorded in both groups and compared using a chi-squared test with alpha risk set at 0.0001 for both interim analyses, according to the method proposed by Peto [32] so as not to change the level of significance of the final primary analysis.

All analyses will be performed under the guidance of the Data Safety Monitoring Board, who will decide on the necessity to recommend premature interruption of the study to the Steering Committee, according to the results of the interim analyses.

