#### Sample size calculation

It has been shown that the mortality of septic shock patients who develop AKI is around 50%. Assuming an absolute reduction in mortality of 10% (55% mortality at 90 days in the delayed RRT group versus 45% in the early RRT group), 864 patients (432 per group) are required to ensure 80% power at a bilateral alpha risk of 0.05, assuming a rate of 5% non-evaluable cases.

The expected reduction of 10% in mortality was chosen as a clinically relevant difference by the study team. There are currently no data in the literature that could serve as a precedent for this, due to wide variations between existing studies in the types of patients included, the definitions of AKI used, and the definition of what constitutes early or late treatment. In light of the heterogeneous data available, a conservative estimate of a 10% reduction was retained as being clinically relevant.

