#### Randomization

Randomization is performed during the first 48 hr of septic shock after the development of at least one criterion defining the failure grade of the RIFLE classification. Randomization takes place after verification of the eligibility criteria, following an online request by the investigator using Tenalea® software (Formsvision BV, Abcoude, Netherlands). This allocation is based on a minimization technique taking into account the center, age, sequential organ failure assessment (SOFA) score, site and type of infection. Patients are randomly assigned to one of the two groups in a 1:1 ratio. Due to the nature of the study intervention, blinding is not possible. However, the CIC-EC (Dijon) will manage all the data and generate blinded reports for the Data Safety and Monitoring Board. The investigators at the participating sites will remain unaware of study group outcomes until the database is locked.

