#### Secondary analyses

1. An analysis identical to the primary analysis, studying mortality at 28 days taking an alpha risk of 0.05.

2. Average length of ICU stay and in-hospital stay will be described and compared for survivors.

3. The number of days without mechanical ventilation and the number of days without RRT in the two groups will be compared. Deceased patients are considered as having a number of days without mechanical ventilation and without RRT equal to zero. The numbers of days will be compared in both groups using a Mann–Whitney test.

4. Dependence on dialysis at hospital discharge will be compared between groups using the chi-squared or Fisher’s exact test. If the groups appear imbalanced in terms of the pre-existence of non-dialyzed chronic renal failure or administration of nephrotoxic drugs, then logistic regression will be performed to adjust for these factors.

5. The frequency of occurrence of at least one episode of hypotension requiring the introduction or increase of noradrenaline, pulmonary edema due to overload, cardiac arrhythmias (ventricular tachycardia, ventricular fibrillation, torsade de pointes and atrio-ventricular block grade III), severe metabolic disorders and blood transfusions (≥3 units of packed red blood cells) will be compared between groups using the chi-squared or Fisher’s exact test.

6. The number and characteristics of patients in the delayed RRT group for whom the occurrence of a criterion for emergency RRT was observed will be described.

These comparisons will be performed by ITT and per protocol. All analyses will be performed using SAS Version 9.2 (SAS Institute Inc, Cary, NC, USA) by the team of statisticians at the CIC-EC of the University Hospital of Dijon, France. The significance level is set at 0.05 for all final analyses.

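### The primary 90-day mortality test ignores the prognostic factors used in the minimisation: it is valid and keeps the planned power, but it is conservative and forgoes about 3 to 8 points of power

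*Protocol article*

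**What the plan says.** In the Protocol article, the Randomization section says that allocation is "based on a minimization technique taking into account the center, age, sequential organ failure assessment (SOFA) score, site and type of infection", in a 1:1 ratio.

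The Statistical analysis section fixes the primary test: "The main comparison of the proportion of deaths at 90 days in both treatment groups will be performed using Fisher’s exact test". It adds that the trial's main conclusion rests on the intention-to-treat analysis alone. Item 1 under Secondary analyses repeats the same analysis for 28-day mortality. That section also sets the level: "The significance level is set at 0.05 for all final analyses".

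Covariate adjustment is mentioned in two places, both secondary and conditional. One is the flexible hazards model, run only if early treatment shows a benefit. The other is a logistic regression for dialysis dependence, run only if the arms look unbalanced on two named factors. Cox regression is listed without covariates.

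The Sample size calculation section assumes "55% mortality at 90 days in the delayed RRT group versus 45% in the early RRT group" and concludes that "864 patients (432 per group) are required to ensure 80% power at a bilateral alpha risk of 0.05, assuming a rate of 5% non-evaluable cases".

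**The concern.** Minimisation makes the arms more alike on the chosen factors than simple randomisation would. If those factors predict death, the difference in death proportions varies less from trial to trial than an unadjusted test assumes. Such a test then rejects less often than its nominal level under the null, and the precision gained by balancing goes unused. Fisher's exact test cannot take covariates and is itself conservative because its p-values are discrete, so the two effects add up.

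The error is on the safe side for false positives. At stake is the chance of detecting a real mortality difference, and the precision of the estimate, in a trial that already records every factor needed for adjustment. The article names the primary test outright, so this is a choice it has made and not a detail left to an analysis plan.

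**Working it through.** **Inputs from the article.** Risks 0.55 and 0.45 (difference d = 0.10, mean 0.50); two-sided alpha 0.05; power 80%; 5% non-evaluable; 432 per arm; 24 ICUs. **Not in the article:** how strongly age and SOFA predict death. This is assumed, as an AUC between 0.50 (no value) and about 0.74.

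**1. Reproduce 864.** Uncorrected formula, per arm:

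n = [1.960 × √(2 × 0.5 × 0.5) + 0.8416 × √(0.55 × 0.45 + 0.45 × 0.55)]² / 0.10² = (1.3859 + 0.5921)² / 0.01 = 391.3, so 392.

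With the continuity correction:

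n_c = (n/4) × [1 + √(1 + 4/(n d))]² = (391.26/4) × [1 + √1.1022]² = 411.0.

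Adding 5%: 411.0 × 1.05 = 431.6, so 432 per arm and 864 in total. Dividing by 0.95, or rounding 411.0 up to 412 first, gives 866 to 868. Starting from the uncorrected 392, the total is only 824 to 826. The article does not name its formula, but 864 fits the corrected one, which approximates Fisher's test.

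**2. Exact behaviour of the test without covariates.** Evaluable patients: 0.95 × 432 = 410 per arm. Summing binomial probabilities over all outcome tables rejected at 0.05:

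| Per arm | Test | Type I error (both 50%) | Power (55% v 45%) |
|---|---|---|---|
| 410 | Fisher | 0.040 | 79.2% |
| 410 | Chi-squared, uncorrected | 0.047 | 81.1% |
| 432 | Fisher | 0.045 | 82.6% |
| 432 | Chi-squared, uncorrected | 0.052 | 84.3% |

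Fisher's test alone therefore costs about 2 points of power, which the size of 864 already covers.

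**3. Behaviour under minimisation.** Simulation with 822 evaluable patients (2 × 411) and 1,500 runs per setting. Minimisation used banded age, banded SOFA, 24 centres and a four-level infection factor, with a 0.8 biased coin. Marginal risks were 55% v 45% for power and 50% in both arms for type I error. Age and SOFA drove death; centre and infection did not. The adjusted model was a logistic regression on arm, age and SOFA. The Monte Carlo standard error is about 1 point for power and 0.5 point for type I error.

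| Assumed AUC | Power: Fisher / chi-squared / adjusted | Type I error: Fisher / chi-squared / adjusted |
|---|---|---|
| 0.50 | 81.3 / 82.9 / 83.8% | 4.0 / 4.3 / 4.6% |
| 0.61 | 81.0 / 82.0 / 84.1% | 2.8 / 3.6 / 4.0% |
| 0.68 | 81.1 / 82.5 / 85.8% | 3.3 / 3.6 / 4.5% |
| about 0.74 | 81.9 / 83.1 / 89.4% | 2.9 / 3.2 / 5.2% |

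Fisher's power is a little above step 2 partly because minimised arms are rarely exactly equal, which makes the test less discrete, and partly by Monte Carlo error. Comparisons should be made within rows.

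**4. Split the gain over Fisher.** For the three AUCs above 0.50:
- Total: 84.1 − 81.0 = 3.1; 85.8 − 81.1 = 4.7; 89.4 − 81.9 = 7.5 points.
- From chi-squared in place of Fisher: 1.0, 1.4 and 1.2 points.
- From adjustment itself: 2.1, 3.3 and 6.3 points.

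At AUC 0.50 a gap of 83.8 − 81.3 = 2.5 points remains. It cannot come from prognostic information and reflects mainly Fisher's conservatism.

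**The case against.** The strongest reply is that nothing promised is broken. The article promises 80% power at two-sided 0.05; Fisher's test delivers about 79% at 410 per arm and 83% at 432, with type I error below 0.05. The test and the sample size also fit each other, since 864 matches a continuity-corrected calculation. All of this stands. A reader might infer that the trial is underpowered, or that patients were recruited for power that will not materialise. The figures do not support that: the loss is a gain above target that is not taken.

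It is also fair that the size of the gain rests on an assumed prognostic strength, that the smallest gains owe much to replacing Fisher's test, and that 410 per arm is the less favourable case, because the plan includes all enrolled patients and death may be known for nearly all of them.

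A further objection is that adjustment needs choices that Fisher's test avoids: an effect measure, a rule for 24 centres and a rule for sparse infection categories. That is right, and the amendment has to settle them. It does not remove the mismatch between an allocation that uses prognostic factors and a primary test that cannot.

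**Conclusion.** The point holds as one of efficiency, not validity. The unadjusted Fisher's exact test keeps the false-positive rate below 0.05 and essentially keeps the planned power. It is conservative: about 0.040 to 0.045 from discreteness alone, and roughly 3 to 4% once minimisation on prognostic factors is allowed for. Compared with an adjusted analysis it forgoes precision and about 3 to 8 points of power.

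The direction is firm. The size depends on an AUC for age and SOFA of about 0.61 to 0.74, which is an assumption, and on a simulation in which centre and infection had no effect on death. The fall in type I error shows no steady trend with prognostic strength beyond Monte Carlo error, so no figure lower than about 3% should be read into it.

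A reader might also infer a problem from the interim analyses, where deaths are "compared using a chi-squared test with alpha risk set at 0.0001 for both interim analyses", while the final test is Fisher's. At that threshold the looks are meant to leave the final level unchanged, and no consequence of the change of test has been shown. It forms no part of this point.

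**What to change.** Amend the protocol before database lock, with the decision taken by people who have not seen outcomes by arm. This needs care because an interim analysis is planned at 200 inclusions and Trial status already reports 200 included.

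- **Primary analysis:** logistic regression of 90-day death on arm, by intention to treat, adjusted for age and SOFA as continuous variables, infection site and type, and centre as a random effect. Test the arm coefficient at two-sided 0.05.
- **Sparse categories:** pool infection categories by a rule written in advance, and state a fallback should the centre effect not converge.
- **Effect measure:** report the standardised (marginal) risk difference with 95% CI, naming the variance method. This keeps the absolute scale on which the trial was sized.
- **28-day mortality:** use the same model.
- **Sensitivity analysis:** keep the unadjusted Fisher's exact test.

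The sample size need not change and no new data are needed, since the factors are recorded for allocation. The cost is a protocol amendment and slightly more analysis work.

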### Study intervention

#### Initiation of RRT

Patients randomized to the early RRT arm will immediately undergo dialysis catheter placement. A maximum of 12 hr is allowed between the diagnosis of AKI and the actual initiation of RRT; this allows for the time required for catheter placement and installation of the RRT equipment, as well as any technical difficulties that may be encountered in clinical practice.

Patients randomized to the delayed RRT group will be closely monitored for 48 hr after randomization to identify as soon as possible the appearance of criteria requiring emergency RRT as defined above. If any of these criteria occur, dialysis catheters are placed and the RRT will be initiated as soon as possible.

In the absence of the appearance of criteria requiring emergency RRT, patients randomized to the delayed RRT group will undergo insertion of the dialysis catheter and initiation of RRT at least 48 hr after the diagnosis of AKI, with a maximum margin of 12 hr allowed (i.e. up to 60 hr maximum), justified by the same technical reasons mentioned above for the early RRT group.

If a patient in the delayed RRT group recovers normal renal function (defined according to the criteria for recovery of renal function listed above) within the 48 hr after randomization, the investigator is free to choose the most suitable treatment and is therefore not obliged to dialyze the patient, but must, in this case, document the absence of RRT and the normalization of renal function.

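### The per-protocol analysis regroups patients by when RRT actually started: an as-treated comparison that moves compliant delayed-arm patients and leaves never-dialysed patients without a group

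*Protocol article*

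**What the plan says.** All references are to the protocol article.

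- **Grouping (Statistical analysis).** "For the per-protocol analysis, patients will be grouped according to the time of initiation of the RRT". The early rule is "If RRT is initiated within 12 hr after the onset of the failure stage according to the RIFLE classification"; the other rule is "if RRT is initiated >12 hr beyond this period, the patient will be included in the delayed RRT group". Neither mentions the allocated arm, and both presuppose that RRT was started.
- **Method (Statistical analysis).** "The per-protocol analysis will use the same techniques as the ITT analysis": Fisher's exact test, Kaplan–Meier, log rank and Cox. Deaths are counted from randomization. No time-dependent exposure, landmark or weighting is named for this analysis.
- **Strategies.** Study design gives the delayed strategy as RRT after 48 to 60 hr, or when emergency criteria appear. Delayed renal replacement therapy gives at least 48 hr, up to 60 hr. Initiation of RRT directs emergency RRT as soon as possible in the delayed arm. For a delayed-arm patient who recovers renal function within 48 hr, it says the investigator "is therefore not obliged to dialyze the patient".
- **Use of the result.** "If the ITT and/or per-protocol analyses show a benefit of early (<12 hr) initiation of RRT, a secondary analysis will be performed". For the secondary outcomes, "These comparisons will be performed by ITT and per protocol". Statistical analysis also limits the main conclusion to ITT.

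**The concern.** A per-protocol set keeps patients in the arm they were randomised to and removes or censors those who departed from it. This rule instead forms groups from an event after randomisation, and prognosis drives that event: the sickest start early on emergency criteria, the best recover and never start, and some die first. Comparing such groups with unadjusted tests does not isolate the effect of timing.

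At stake are a mortality comparison published under a misleading label, the same regrouping of every secondary and safety comparison, and a further model that can be launched on the strength of it. The Discussion says emergency criteria arising after randomization pose no problem. That is right for ITT but not for this regrouping.

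**Working it through.** **1. The rule set beside the strategies**

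| Patient | Followed the allocated strategy? | Group under the rule |
|---|---|---|
| Early arm, RRT within 12 hr | Yes | Early |
| Early arm, RRT later | No | Delayed (moved) |
| Early arm, dies before RRT within the window | No departure | None |
| Delayed arm, RRT at 48–60 hr | Yes | Delayed |
| Delayed arm, emergency RRT within 12 hr of failure onset | Yes | Early (moved) |
| Delayed arm, emergency RRT at 13–47 hr | Yes | Delayed (correct) |
| Delayed arm, non-emergency RRT after 12 hr but before 48 hr | No | Delayed |
| Delayed arm, recovers, no RRT | Yes | None |
| Delayed arm, dies before RRT was due | Yes | None |

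Three kinds of delayed-arm patient who followed the protocol are moved or have no group, while two kinds of departure count as delayed.

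**2. The cut-off.** "Conversely, if RRT is initiated >12 hr beyond this period, the patient will be included in the delayed RRT group" can mean more than 12 hr after failure onset, or more than 12 hr after the first 12 hr, i.e. beyond 24 hr. On the second reading, starts between 12 and 24 hr have no group either.

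**3. Size with no true effect.** The documents give only the design: 432 per group, 55% versus 45% mortality, a 10-point effect. The sample size reproduces closely: 412 evaluable per arm with continuity correction, 412/0.95 = 433.7, so 434 per arm or 868 against 864. It is not at issue.

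Everything else here is assumed. Take mortality m = 0.50 in both arms, with every early-arm patient starting within 12 hr. In the delayed arm, a share D dies before RRT, R recovers without RRT (mortality r), and E has emergency RRT within 12 hr (mortality e).

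- Early = (m + E·e)/(1 + E)
- Delayed, never-RRT dropped = (m − D − R·r − E·e)/(1 − D − R − E)
- Delayed, never-RRT kept = (m − E·e)/(1 − E)

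| Case | Early | Delayed, dropped | Difference (early minus delayed) | Delayed, kept | Difference |
|---|---|---|---|---|---|
| A: D 8%, R 15% (r 30%), E 10% (e 65%) | 0.565/1.10 = 51.4% | 0.31/0.67 = 46.3% | +5.1 | 0.435/0.90 = 48.3% | +3.0 |
| B: as A, D 12% | 51.4% | 0.27/0.63 = 42.9% | +8.5 | 48.3% | +3.0 |
| C: D 5%, R 30% (r 20%), E 0 | 50.0% | 0.39/0.65 = 60.0% | −10.0 | 50.0% | 0 |

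Positive differences count against early RRT. Case A without emergency starts, dropped, gives 0.375/0.77 = 48.7% against 50%: 1.3 points.

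**4. Each mechanism alone**, with 432 per arm, m = 0.50, 1% of the early arm dying before RRT, and never-RRT patients dropped. The last column is the approximate chance of a significant result at two-sided 0.05.

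| Mechanism in the delayed arm | Difference, points | False-positive chance |
|---|---|---|
| 5 / 10 / 15% die before RRT | +2.1 / +5.1 / +8.3 | 9 / 30 / 65% |
| 5 / 15 / 25% recover (25% mortality), 1% die before RRT | −1.3 / −4.4 / −8.3 | 7 / 23 / 61% |
| 5 / 10% emergency RRT within 12 hr (70% mortality), 1% die before RRT | +2.1 / +4.2 | 9 / 23% |

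Mixtures of the three, with 3% of the early arm starting late, run from −3.5 to +11.7 points and leave 48 to 134 patients without a group. Keeping delayed-arm never-RRT patients in the delayed group reduces the first two rows to about −0.5 points, but leaves +1.5 or +3.6 in the third.

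**The case against.** The strongest reply is that this is a secondary analysis and that some harsher readings fail. Most of that stands.

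- **A reader might infer that the trial's result is compromised.** It is not. The primary analysis is ITT and the main conclusion rests on it alone. The primary test, sample size and interim rules do not use this grouping.
- **A reader might infer that the per-protocol result decides whether the timing model is run.** The condition is ITT and/or per protocol, so a per-protocol benefit is sufficient but not necessary. The model is itself secondary, uses exact start times and adjusts for major confounders.
- **A reader might infer that every start at 13–47 hr is misclassified.** Study design makes an emergency start in that interval compliant with the delayed strategy. Only early-arm late starters and non-emergency delayed-arm starts before 48 hr are misplaced.
- **A reader might infer that the plan drops never-RRT patients.** The article is silent, and a condensed article may leave their placement to a fuller document. This matters: kept in the delayed group, case C falls from 10 points to zero and cases A and B to about 3.
- **A reader might infer that emergency-triggering safety events generally migrate to the early group.** They do so only when RRT starts within 12 hr of failure onset. The safety comparisons are also done by ITT, and delayed-arm patients meeting emergency criteria are described separately.
- **The assumed rates may be generous.** Patients needing emergency RRT before randomization, or expected to die within 24 hr, are excluded. The 12 hr clock starts at failure onset, so less than 12 hr may remain after randomization.

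What the reply does not answer is that the grouping rule itself is stated in the article. It ignores allocation, moves compliant emergency starters whatever is done with never-RRT patients, and is paired with unadjusted techniques.

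**Conclusion.** The concern holds for the per-protocol analyses only. As written they are as-treated comparisons, biased in a direction that cannot be known in advance: losing deaths before RRT, or moving emergency starters to early, makes early RRT look worse, while losing recoverers makes it look better.

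In the worked cases with no true effect, the spurious difference is about 3 points with never-RRT patients kept in the delayed group and 10% receiving emergency RRT within 12 hr. It is roughly 5 to 10 points, either way, with them dropped. Lower rates, or mechanisms that offset each other, give less. These figures show what the rule can do against a 10-point design effect. They do not predict this trial, because none of the rates comes from the documents.

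**What to change.** Define the per-protocol set within the randomised arms, never move a patient to the other arm, and handle death the same way in both:

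- **Early arm:** RRT started within 12 hr of AKI diagnosis, or death before that window closed.
- **Delayed arm:** RRT at 48–60 hr, or emergency RRT on a protocol criterion, or documented recovery without RRT, or death before RRT was due.

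The symmetry matters. Keeping delayed-arm deaths before RRT while excluding early-arm ones would itself favour early RRT.

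If the observed-timing comparison is kept, label it as-treated and exploratory, retain all patients including those who never start RRT, and treat RRT start as a time-dependent exposure or use clone-censor-weighting. Run the exact-timing model whatever the ITT or per-protocol result, also labelled exploratory. Reconcile the 12 hr cut-off in Statistical analysis, including its ambiguous wording, with Study design, Delayed renal replacement therapy and Initiation of RRT.

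The cost is wording and some extra programming on data already planned for collection. The revised set still selects on adherence, so it should remain supportive of ITT.

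### The exact-timing survival model is fitted only after a result favouring early RRT, so the timing curve is reported from data selected for apparent benefit and withheld otherwise

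*Protocol article*

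**What the plan says.** All of the following is in the protocol article, mostly under Statistical analysis.

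- **Unconditional analyses.** The primary test comes first: "The main comparison of the proportion of deaths at 90 days in both treatment groups will be performed using Fisher’s exact test". The survival methods follow in the same sentence, and no condition is attached to them either: "with secondary analysis by the Kaplan–Meier method, comparison using the log rank test, and Cox regression". The per-protocol analysis repeats these techniques.
- **Per-protocol grouping.** Patients are sorted by when RRT actually began. A start within 12 hr of reaching the failure stage counts as early and a later start as delayed, whatever the allocation.
- **Conditional analysis.** "If the ITT and/or per-protocol analyses show a benefit of early (<12 hr) initiation of RRT, a secondary analysis will be performed". The model is an extension of proportional hazards intended "to estimate the non-proportional and non-log-linear effects, taking into account the exact time since initiation of RRT". Its stated use is one of "thus visualizing whether early initiation results in lower risk of death after adjusting for major confounders".
- **Scope.** "The main conclusion of the test will only cover the ITT analysis".

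Three other sections bear on the point. The Objectives ask whether timing affects 90-day mortality and give no direction. The Sample size calculation uses a two-sided alpha of 0.05. The Background cites a retrospective study in which mortality was U-shaped in the timing of RRT.

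**The concern.** The exact-timing model is the only listed analysis that treats RRT start as a continuous quantity, so it speaks most directly to the question of when to start. The rule that decides whether it is fitted looks at the result first and accepts only one direction. This has two consequences.

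1. When the curve is reported, it is estimated on data already known to favour early RRT, by ITT or per protocol. Part of that apparent advantage is selection, and a reader of the curve cannot see how much.
2. When early RRT looks neutral or harmful, no curve is planned. Those are cases where the shape of the timing effect would also be informative, given the U-shaped association that the article itself cites.

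The *and/or* widens the condition. A per-protocol benefit is enough even when the randomised comparison shows none, and the per-protocol groups do not have the protection of randomisation.

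**Working it through.** **Step 1: reproduce the plan's own figure.** Inputs from Sample size calculation: 55% versus 45% mortality, 80% power, two-sided alpha 0.05, 5% non-evaluable.

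- Uncorrected n per arm = [1.96·√(2·0.5·0.5) + 0.8416·√(0.55·0.45 + 0.45·0.55)]² / 0.10² = (1.386 + 0.592)² / 0.01 ≈ 391.3, so 392.
- With continuity correction: (392/4)·[1 + √(1 + 4/(392·0.10))]² = 98·(2.0498)² ≈ 411.8, so 412 per arm and 824 in total.
- Allowing for 5% non-evaluable: 824/0.95 gives 868, or 824·1.05 gives 866. The stated 864 is reproduced to within rounding. Without the correction the total is 826.

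The sample size is not in dispute. It fixes the range for the next step: 432 per arm randomised, or 432·0.95 ≈ 410 evaluable.

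**Step 2: how often the ITT result triggers the model.** Assumption: showing a benefit means Fisher two-sided p<0.05 with fewer deaths in the early arm. Each scenario was simulated 20,000 times at 410 and at 432 per arm.

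| True 90-day mortality, early vs delayed | Model triggered | Mean observed early advantage when triggered | Significant harm found by ITT |
|---|---|---|---|
| 45% vs 55% | 80–82% | about 11 points | 0% |
| 47.5% vs 52.5% | 27–30% | about 9 points | under 0.1% |
| equal (50% or 55%) | 1.9–2.4% | about 8 points | 1.9–2.3% |
| 52.5% vs 47.5% | about 0.03% | too few runs to use | 27–29% |
| 55% vs 45% | 0 of 20,000 | none | 79–83% |

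**Step 3: check the null row by hand.** At 432 per arm and 50% mortality, SE = √(2·0.25/432) = 0.0340.

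- The trigger needs a difference beyond 1.96·0.0340 = 6.7 points.
- By the normal approximation this happens in 2.5% of trials in the favourable direction. Fisher's test is somewhat conservative, hence about 2%.
- The mean difference given that it happens is SE·φ(1.96)/0.025 = 0.0340·0.0584/0.025 ≈ 0.079, or about 8 points.

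**Step 4: sensitivity to the undefined term.** If a favourable point estimate were enough, the trigger would be met in about 48–49% of trials with no true difference, with a mean apparent benefit just under 3 points. The selection is then weaker but still one-directional.

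**Step 5: the per-protocol route.** Because the two routes are joined by *and/or*, adding the second can only raise the chance that the model is fitted. By how much cannot be computed, since the article gives no rates of emergency RRT, recovery or death before RRT. Under Initiation of RRT, the investigator treating a delayed-arm patient who recovers "is therefore not obliged to dialyze the patient", and the grouping rule gives such a patient no start time.

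The direction of any distortion depends on how these patients are handled. Take no RRT effect, 50% mortality with front-loaded deaths, 20% emergency RRT in the delayed arm and 20% of the remainder never dialysed (all assumed). Counting only RRT recipients gives about 49.1% mortality for starts within 12 hr versus 46.3% for later starts. Counting non-recipients as delayed gives about 49.1% versus 51.0%. The sign reverses, so no size is claimed for this route.

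**The case against.** The strongest reply is that this is an openly prespecified secondary model, that the main conclusion is confined to ITT, and that Fisher's test, log rank and Cox regression are run without any condition. All of that stands, and it limits the point. If early RRT truly were 10 points worse, the ITT test would find significant harm in about 79–83% of trials. Only the timing curve would be missing.

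Three stronger readings are tempting, and the article does not support them.

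- *A reader might infer that harm or no effect is never modelled.* That is true only of the exact-timing model. The group comparisons are two-sided and unconditional.
- *A reader might infer that the curve can only support early RRT.* The model is chosen because it allows non-proportional and non-log-linear effects. Once fitted, it could show a flat, U-shaped or time-limited curve. The condition selects the data; it does not fix the shape.
- *A reader might infer that the model compares only patients who survived to RRT, and so flatters early starts.* The article does not restrict it to recipients. The phrase "taking into account the exact time since initiation of RRT" can be read as a quantity that changes during follow-up. Coding of exposure and the list of confounders are normal content for an analysis plan, which is not shown here. Nor would the bias necessarily favour early RRT, as Step 5 shows.

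The reply does not justify the condition itself. Announcing a result-dependent rule in advance does not remove the selection it causes, and the article gives no reason for fitting the model in one direction only.

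**Conclusion.** The point holds for the trigger alone. The article ties its exact-timing model to a favourable result, in one direction, by a route that need not be randomised.

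With benefit read as two-sided p<0.05, the ITT route yields the curve in about 2% of null trials (mean apparent advantage about 8 points), in about 80% if early RRT is 10 points better, and essentially never if it is 10 points worse. These figures rest on that reading, on 410 to 432 patients per arm, and on the ITT route only. The per-protocol route can add to them by an amount the article does not allow one to estimate.

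Primary type I error, power and the main conclusion are untouched. What changes is what the trial can credibly report about the shape of the timing effect. The correction is worth making because it is cheap and specific.

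**What to change.** Delete the condition. State that the flexible timing model will be fitted and reported whatever the direction or significance of the ITT and per-protocol results, and label it exploratory.

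The same sentence can usefully say that all randomised patients are included and that RRT start is handled as time-dependent, so that never-dialysed patients and deaths before RRT stay in the analysis. The second part is a clarification, which the analysis plan may already contain; it does not correct a stated error.

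Cost: about one sentence and a little more analysis work, with no change to sample size or alpha. The downside is one more exploratory result to report and interpret if the trial is neutral or shows harm.
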